**2.2. Study variables**

The study variables are the socio-demographic characteristics, time, cost incurred during tuberculosis case detection, follow up and treatment. In addition cost related to supervision and monitoring and evaluation of tuberculosis control programme in the study sites will be included.

**2.3. Data collection techniques and tools**

Trained data collectors will administer a pre-tested structured questionnaire. Study variables include socio-demographic variables of tuberculosis patients, financial expenses and time. When the tuberculosis patient is less than 18 years, the data collectors will interview the parents or the guardians accompanying them to health institution. The data collectors will review financial reports of health institutions and the district.

**2.4. Sample size calculation**

Community based tuberculosis care reduced 30% of patient cost in health facility to 13 % in community-based tuberculosis treatment in a study conducted in Tanzania.[34] Based on this

n = [(z1 + z2)*2*P]/

n = the sample size from each district z1 =level of significance of 95 %( 1.96)

z2 =power of the study of 90 %( 1.28) p1 = patient cost in facility based tuberculosis treatment (30%)

p2 = patient cost in community-based tuberculosis treatment (13%)

P= the average proportion of treatment success in the control and intervention groups (21.5%)

n = = = 123

IF = 1 + (m-1)*ICC

IF - inflation factor or design effect m - number of cluster size 15 assuming equal cost per cluster

ICC - intracluster correlation coefficient assuming typical ICC of 0.04

IF = 1 + (m - 1)*ICC = 1 + (15 - 1) * 0.04 = 1.56

Effective sample size = IF * calculated size = 1.56* 123 = 192

In addition, the cost related to tuberculosis treatment supervisors, community health agents, tuberculosis programme coordinators in the district and health institution will be included.

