In a study conducted in Uganda, they evaluated conventional hospital-based and community-based tuberculosis treatment for all tuberculosis patients. They admitted all smear positive tuberculosis patients in hospital for two months. Community based approach reduced the total cost per patient treated successfully by 43 % and increased success rate of smear positive tuberculosis patients by 19 %. The main drop in cost was because of the decreased duration of hospital admission from two months to nineteen days on average.[33] This mainly focused on hospital settings. Therefore, the cost of treating tuberculosis patients at health centre level needs further analysis.

An individual randomized controlled trial study conducted in Tanzania found that community-based tuberculosis treatment reduced cost per tuberculosis patient successfully treated by 35 % with similar treatment outcomes. The main cost drop was because of fewer visits to tuberculosis clinic. They recommended applicability of community based tuberculosis care in resource limited settings.[34] Before applying to a wider set-up, they should further evaluate the applicability at community level.

The World Bank reported that tuberculosis control programme as a cost-effective health intervention. [35] Different studies showed that community-based tuberculosis care is better than the existing conventional tuberculosis care. It also showed that it is less costly per patient treated and as effective or more compared to all alternative approaches [9, 36]. Therefore, this could be a better and feasible option in resource-constrained countries with high tuberculosis burden and overstretched health care.

In summary, community-based approach compliments the conventional facility based treatment. It minimizes cost per patients treated successfully and reduces the work burden on health workers. It is equally acceptable as health facility based treatment[37], improves patient adherence to treatment, and follow-up. Moreover, by incorporating simple symptom score, community health workers could assist in tuberculosis case finding and sputum collection and transport. Therefore, tuberculosis control programme should explore ways of improving community-based tuberculosis care in different settings.

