**Study - III**

This is a randomized controlled community trial to find out the cost per tuberculosis patient treated successfully. The study follows societal perspective of cost analysis. The main cost items related to the costs of tuberculosis prevention and control programme will be collected as for diagnosis, follow up and supervision including patient and community health workers time and costs. Data collectors will also get records from district finance offices. The data collectors will calculate cost of time based on monthly salary of health workers and tuberculosis patients if they are in the productive age groups. In addition, the cost of the person accompanying the patient will be included. The outcome indicator for the study is the cost per patient treated successfully.

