**2. Methods**

**2.1. Study design**

This is a randomized controlled community trial to find out the costs per tuberculosis patient treated successfully in the intervention and non-intervention districts. Cost related to tuberculosis control programme in the study sites will be determined according to the actual expenses and time cost. Programme coordinators, health workers, community health agents, tuberculosis treatment supervisors, tuberculosis patients and relatives accompanying them to health facilities in the study sites will be included in the study.

The cost analysis will follow societal perspective to analyse the cost per patient. The data collectors will obtain financial reports from districts and health institutions finance sections to collect expenditures for tuberculosis control programme, health workers and community health agents’ time and costs associated to tuberculosis prevention and control activities. In addition, they will collect cost of the patient and the relative who accompanied them during their visit to health institutions.

The investigator will use cost per tuberculosis patient successfully treated as an outcome measure. Future cost and productivity gains will not be included in the study. Standard cost estimation of all expenses and time of the patient, treatment supervisor and health workers will be done. Data collectors will use a structured pre-tested questionnaire for data collection.

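### Study III is sized with a two-proportion formula fed with cost percentages, so its 90% power and 192 per group have no basis for a cost outcome

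*Protocol*

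**What the plan says.** The general description of Study III in section 6.2 states: "The outcome indicator for the study is the cost per patient treated successfully". Study Three, section 2.1, repeats this: "The investigator will use cost per tuberculosis patient successfully treated as an outcome measure". The same section sets the scope: "The cost analysis will follow societal perspective to analyse the cost per patient". Programme, health worker, community agent, patient and accompanying-relative costs are all to be counted.

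Study Three, section 2.4, takes its effect from a cited Tanzanian study: "Community based tuberculosis care reduced 30% of patient cost in health facility to 13 % in community-based tuberculosis treatment". The inputs are then "p1 = patient cost in facility based tuberculosis treatment (30" per cent and "p2 = patient cost in community-based tuberculosis treatment (13" per cent. Their mean is labelled "P= the average proportion of treatment success in the control and intervention groups (21.5" per cent. With z-values of 1.96 and 1.28 (90% power) the section obtains 123. It multiplies by 1 + (15 - 1) x 0.04 = 1.56 and arrives at 192.

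The literature review, citing the same Tanzanian source, reports that "community-based tuberculosis treatment reduced cost per tuberculosis patient successfully treated by 35 % with similar treatment outcomes". Section 2.4 does not use that figure.

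**The concern.** A two-proportion formula takes its variance from P(1-P), the variance of a yes/no outcome. Here p1 and p2 are percentages describing patient cost. Neither is a fraction of patients who experience something, so P(1-P) is not the variance of anything Study III measures. The precision of a cost comparison depends on the spread of cost between patients and between clusters, and the section states neither.

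The effect size also belongs to a different quantity. The 30% and 13% concern patient cost, whereas the outcome is societal cost divided by the number of successes.

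Cost per success is the only outcome named for Study III, and finding it is one of the five specific objectives. A reader would judge the result, in particular a non-significant difference, against a 90% power claim that was not derived for it.

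**Working it through.** **1. Reproducing the protocol's figure.** The printed formula is incomplete in the available text, but the results identify it as the pooled two-proportion formula. Inputs from Study Three, section 2.4: p1 = 0.30, p2 = 0.13, P = 0.215, z1 = 1.96, z2 = 1.28.

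- (1.96 + 1.28)² = 10.4976
- P(1-P) = 0.215 x 0.785 = 0.1688
- n = 10.4976 x 2 x 0.1688 / 0.17² = 122.6, rounded up to 123
- 123 x 1.56 = 191.9, rounded up to 192

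Both figures reproduce. The power of 123 effective patients per group is 90.6% for comparing 30% with 13% of patients having an event, and that is the only comparison to which the 90% applies. The section defines n as the sample from each district. I read this as each group, because section 2.1 compares intervention with non-intervention districts.

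**2. What 192 per group gives for a cost.** The effective size is 192 / 1.56 = 123.1 per group. Assumptions, none of them in the section: a 35% fall in mean cost per patient (the literature review's figure, borrowed for illustration), CV of 1.0 or 1.5, the protocol's design effect carried over to cost, and two-sided 5%. The control mean is set to 1. Three ways of treating the spread:

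- Equal SD in both arms: z = 0.35 x √(123.1/2) / CV - 1.96
- Equal CV in both arms: z = 0.35 x √(123.1/(1 + 0.65²)) / CV - 1.96
- Log cost, log-normal with equal CV: z = |ln 0.65| x √(123.1/(2 ln(1 + CV²))) - 1.96, with |ln 0.65| = 0.431

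| Assumption | CV 1.0: z, power | CV 1.5: z, power |
|---|---|---|
| Equal SD | 0.79, 78% | -0.13, 45% |
| Equal CV | 1.30, 90% | 0.21, 58% |
| Log cost | 2.10, 98% | 1.15, 87.5% |

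Number per group for 90% power, after the 1.56 design effect:

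- Equal SD, 2 x 10.4976 x (CV/0.35)² x 1.56: about 267 at CV 1.0 and 602 at CV 1.5
- Equal CV, 10.4976 x CV² x 1.4225 / 0.35² x 1.56: about 191 and 428
- Log cost, 2 x 10.4976 x ln(1 + CV²) / 0.431² x 1.56: about 123 and 208

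**3. Dependence on what 30% to 13% means.** With equal SDs, if the change is read as a relative fall of 17/30 = 56.7%, power is 99% at CV 1.0 and 84% at CV 1.5. If it is read as a fall of 17% of the control mean, power is 27% and 14%.

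The same 192 patients per group can therefore be ample or far too few, depending on inputs that the protocol does not give.

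**The case against.** The strongest reply is that little in the trial depends on this calculation. The objective of Study III is to find out a cost, and no hypothesis test is stated for it. The trial's size comes from Study Two, which asks for 255 per group on its own binary outcome. That exceeds 192 and owes nothing to the Study III calculation. This stands, and it limits the severity. It does not rescue the 90% figure, which the protocol states for this study.

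The wrong label on P also proves little by itself. It matches the Study Two wording, looks carried over, and changes no number.

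A reader might go further and infer that Study III is underpowered and likely to miss a true saving, because costs are usually skewed. The documents do not support that. The low powers (78% at CV 1.0, 45% at CV 1.5) require the intervention arm to keep the control arm's SD while its mean falls by 35%. If the CV is held equal instead, 192 is almost exactly what 90% power needs at CV 1.0. On log cost it exceeds that need at CV 1.0. These alternatives are assumptions too, and log cost compares geometric means rather than cost per success. Together they show that the direction of the mis-sizing is open.

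**Conclusion.** The point holds as a mismatch between formula and outcome. It is not an arithmetic error and does not show a shortage of patients. The figures 123 and 192 follow from their inputs, but the inputs are cost percentages treated as event proportions, and no measure of cost variation is used. The 90% power claim for Study III is therefore unfounded as written.

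The size of the error cannot be fixed at one number. Under an assumed 35% fall in mean cost, power with 192 per group runs from about 78% to 98% at CV 1.0 and from about 45% to 87.5% at CV 1.5. These ranges rest on the assumed CVs, on applying an ICC of 0.04 to cost, and on using mean cost per patient as a stand-in for cost per success. The stand-in is reasonable only if success rates are similar in the two arms. Severity: should-fix.

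**What to change.** In Study Three, section 2.4, delete the two-proportion calculation and the 90% power statement, including the label that calls 21.5% a treatment success proportion. Then take one of two routes.

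- **Estimation.** State that Study III estimates cost per success in each group and the difference between groups, with a cluster-based interval (for example a cluster bootstrap) at the planned number of patients, and make no power claim.
- **Restated power or precision.** Name the cost quantity (patient cost, or societal cost per success). Take the effect size for that same quantity, and give the power or interval width that 192 per group provides over a declared range of CV and of ICC for cost. The 35% reduction applies to cost per success and should not be paired with an SD of patient cost alone. The questionnaire pretest is a doubtful source for that SD: section 6.5 describes it only as a practical session within data-collector training and gives no sample size.

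Either route means rewriting one paragraph, with no extra patients. The price is a less definite figure: a range, or an interval with no power statement, in place of a single number.

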**STUDY FOUR - TO FIND OUT THE ACCEPTABILITY OF COMMUNITY BASED TB CARE**

**1. Objective**

- to assess acceptability of community based tuberculosis care

**2. Methods**

**2.1. Study design**

This is a cross-sectional study to find out the acceptability of community based tuberculosis care. The study will include all health workers (health professionals, health extension workers and community health agents), community members, and tuberculosis patients who completed their treatment (ex tuberculosis patients) in the study sites. Based on the sample size, study subjects will be randomly selected from all intervention clusters. Community members next to treated tuberculosis patients will be included in the study. Next fifth household on the right side of treated tuberculosis patients’ house will be included. Health workers working in tuberculosis clinic, health extension workers and tuberculosis treatment supervisors will be included in the study.

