**Study - IV**

This is a cross-sectional study to find the acceptability of community based tuberculosis care by health workers, community members, and tuberculosis patients. Health workers, tuberculosis patients and community members will participate in the study districts. The data collectors will randomly select tuberculosis patients, health workers, health extension workers, tuberculosis treatment supervisors and community health agents who are directly involved in tuberculosis patient care. From the community previously treated tuberculosis patients and community members living closer to tuberculosis patients, next fifth household heads will be taken. Trained data collectors will administer a pretested questionnaire about the acceptability of community-based TB care.

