**2.3. Data collection techniques and tools**

Data collectors will find the names of ex tuberculosis patients from tuberculosis unit registers and list them out according to the study clusters. Based on the number and sample size they will randomly select ex tuberculosis patients from all intervention cluster to participate in the study.

During data collection if they found that the ex tuberculosis patient has died or moved to other community they will replace her/him by next ex tuberculosis patient on the list. If they come across ex tuberculosis patient less than 18 years old, they will interview head or guardian of the household.

In addition to find out the acceptability by the community, data collectors will interview household next to ex tuberculosis patients household if they know about tuberculosis treatment. If they do not know will proceed on the next right side household and interview guardian head of the household.

A standardized pretested questionnaire including socio-demographic variables and factors affecting acceptability will be included in the questionnaire. Programme coordinators and the investigator will give training to health workers about administering the questionnaire. Trained data collectors will administer the interview preferably by those who can speak the local language.

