**2.4. Sample size calculation**

In a study conducted in the Tigray, northern part of Ethiopia, it showed that 64.5 % community health workers accepted community based tuberculosis care. [38]

n =

Where: n = the sample size

p = the proportion of tuberculosis patients who accepted community-based tuberculosis care

q = 1- p z = the percentage level at 95% confidence interval (1.96)

d = the margin of error = 5% Based on this

n = = 351

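### Study IV can select only patients who completed treatment, so acceptability among tuberculosis patients is probably overstated, by an amount the protocol does not let one determine

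*Protocol*

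**What the plan says.** The operative text is in Part Two, Study Four. Section 2.1 describes the patient group as "tuberculosis patients who completed their treatment (ex tuberculosis patients"); the parenthesis in effect defines the term. Section 2.3 then builds the sampling list from that term: "Data collectors will find the names of ex tuberculosis patients from tuberculosis unit registers and list them out according to the study clusters". Selection is random but confined to the intervention arm: "they will randomly select ex tuberculosis patients from all intervention cluster to participate in the study". A sampled person who "has died or moved to other community they will replace her/him by next ex tuberculosis patient on the list".

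Other parts of the protocol describe the patients more broadly. The sample size in Study Four, section 2.4 defines its target as "p = the proportion of tuberculosis patients who accepted community-based tuberculosis care", with no condition on completion. Part One, section 6.2 (Study - IV) says "The data collectors will randomly select tuberculosis patients, health workers, health extension workers, tuberculosis treatment supervisors and community health agents" and adds: "From the community previously treated tuberculosis patients and community members living closer to tuberculosis patients, next fifth household heads will be taken". Neither sentence requires completed treatment. The summary table in section 5.2 gives the Study IV population simply as health workers and TB patients.

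The annexed treatment outcome questionnaire records cured, treatment completed, died, defaulted, failure and transfer out as separate outcomes. Non-completers are therefore identifiable in the trial's own records.

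**The concern.** Completing months of supervised treatment is partly a consequence of finding its delivery tolerable. A patient sample restricted to completers is thus selected on something plausibly related to the answer it is asked to give. Those who defaulted or stopped are natural candidates for a negative answer, and the annexed acceptability form asks people who answer No for their reasons, offering stigma, drug storage and professional incompetence. Under sections 2.1 and 2.3 these patients have no chance of being asked.

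The protocol also treats poor adherence as one of the problems behind the project (sections 2 and 4). An acceptability figure that leaves out patients who did not adhere is of limited use for that purpose. A larger sample would not help, because it would only narrow the interval around the completers' proportion.

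Separately, the sections disagree on who the patients are, and data collectors could follow either version.

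**Working it through.** **The plan's own figure.** Study Four, section 2.4 uses p = 0.645, z = 1.96 and d = 0.05. Then n = z² × p × (1 − p) / d² = 3.8416 × 0.645 × 0.355 / 0.0025 = 351.85, against 351 stated. The figure reproduces, apart from truncation. The 64.5% was observed in community health workers, so it says nothing about patients by treatment outcome.

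**Bias formula.** Let s be the share of patients who complete, A the acceptance among completers and B the acceptance among non-completers. Acceptance in all patients is s × A + (1 − s) × B, while the planned sample estimates A. The bias is therefore (1 − s) × (A − B).

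**Share not completing.** Study Two, section 2.4 plans 85% treatment success in the intervention group. Section 1.3 counts cured and completed together as success, so I use success as the measure of completion. This gives 1 − s = 0.15. It is a ceiling at that success rate, because non-success includes deaths, transfers and failures as well as defaulters.

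**Acceptance gap (assumed).** The documents give no value for A or B. I take A = 75% and B = 20% to 50%, a gap of 25 to 55 points.

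| Case | Non-completer share | Gap 25 points | Gap 55 points | Gap giving 5-point bias |
| --- | --- | --- | --- | --- |
| All non-successes interviewable | 0.15 | 3.75 points | 8.25 points | 0.05 / 0.15 = 33 points |
| Half interviewable (assumed) | 0.075 / (0.85 + 0.075) = 0.081 | 2.0 points | 4.5 points | 0.05 / 0.081 = 62 points |

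**Sensitivity to A.** With A = 64.5% and B = 20% to 60%, the bias at a share of 0.15 runs from 0.15 × 4.5 = 0.7 points to 0.15 × 44.5 = 6.7 points. If A = B, it is zero.

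**The case against.** The best counter-argument is that the wording is loose. Study Four uses completed, ex and treated patients almost interchangeably, and the outcome form lists cured apart from treatment completed, so completed might only mean no longer on treatment. The reading is strained. Section 2.1 states completion and ties the term ex patient to it, section 2.3 samples on that term, and nothing in Study Four brings defaulters in. If that was the intention, the text still needs correcting.

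Several stronger readings are tempting, and the documents do not support them.

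- A reader might infer that patients who refused community supervision are excluded. They are not: section 2.1 requires completed treatment in the study sites, not treatment under a community supervisor. Someone who declined a supervisor and finished at a facility is eligible.
- A reader might take the non-completer share as 30%, from the 70% success rate of Sidama zone, and obtain 0.30 × 25 = 7.5 to 0.30 × 55 = 16.5 points. But 70% is the control assumption, and only intervention clusters are sampled. That range would apply only if the intervention had no effect on treatment success.
- A reader might infer that the question on reasons for a No answer will have almost no respondents. At 75% acceptance, 25% answer No, which is about 88 people if all 351 were patients. Section 2.4 does not say how the 351 divide among groups. What is lost is the reasons of defaulters, not all negative answers.
- A reader might infer that the whole study is affected. Health workers and treatment supervisors are sampled separately. Community households are located from treated patients' houses and so follow the same list, but the documents do not show that this biases their answers.

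It also stands that default need not mean rejection of community care, and that the dead cannot be interviewed under any design.

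**Conclusion.** The point holds for the patient stratum. As written, Study IV cannot select intervention-cluster patients who defaulted or stopped, while its stated target is tuberculosis patients without that restriction. Upward bias is likely but not demonstrated, because it rests on non-completers accepting the service less often than completers do. Under the assumptions above, it can exceed the stated 5-point margin only if most non-successes could have been interviewed and the gap is at least about 33 points. If half are reachable, the assumed gaps keep it below that margin. The disagreement between sections is a fault in its own right and needs no assumption. This is a secondary cross-sectional study, and the randomised comparison of treatment outcome is untouched.

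**What to change.** Draw the patient sample at random from all patients registered in the intervention clusters in the TB unit registers, whatever their treatment outcome, explicitly including those who defaulted or stopped. Record each selected patient's outcome from the register. Report acceptability overall and by outcome, with the number selected but not traced and the number replaced. The last count matters because the replacement rule could otherwise quietly swap hard-to-find defaulters for completers.

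Make the summary table, section 6.2 (Study - IV) and Study Four, sections 2.1, 2.3 and 2.4 name the same patient population, and say whether patients still on treatment belong to it. If completers alone are intended, the target in section 2.4 and the stated conclusion must say so.

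The cost is a change of wording and some extra tracing of defaulters, which will not always succeed. The registers are already the source of names and outcomes are already recorded, so no larger sample is needed.
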